**Discussion:**

Based on our previous study, the initial dose of AMR 25 mg/m^2^ is expected to be tolerated and acceptable. Here, we aim to determine whether treatment with AP and concurrent AHTRT would be an optimal choice with manageable toxicities for LD‐SCLC.

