**FIGURE 1 tca14555-fig-0001:**
[figure not shown]
In the first cycle, AMR 25 (or 20, if reduced) mg/m^2^/day (from day 1 to day 3) and cisplatin 60 mg/m^2^/day (day 1) will be administered. In the following three cycles, AMR 35 mg/m^2^/day (from day 1 to day 3) and cisplatin 60 mg/m^2^/day (day 1) will be administered. The accelerated hyperfractionated thoracic radiotherapy, as 1.5 Gy/time, twice daily, 5 days a week, 45 Gy in total, will be administered concurrently from day 2 of the first chemotherapy cycle

MTD and RD will be determined as shown in Figure 2. (1) If DLTs are not observed in the initial three patients, we plan to add six patients as the extension study. The 25 mg/m^2^ of AMR will be determined as MTD and RD. (2) If DLTs are confirmed in one of the first three patients enrolled, we will add three additional patients at 25 mg/m^2^ of AMR to evaluate DLTs further. (2)‐1: If DLTs are confirmed in none of the additional three patients, we will add six additional patients as the extension study. The 25 mg/m^2^ of AMR will be determined as MTD and RD. (2)‐2: If DLTs are confirmed in more than one of the additional three patients, the study will be finished. The 25 mg/m^2^ of AMR will be determined as MTD and the 20 mg/m^2^ of AMR will be determined as RD. (3) If DLTs are confirmed in more than two of the first three patients, we plan to add three patients to receive a reduced dose of 20 mg/m^2^. (3)‐1: If DLTs are confirmed in none of the additional three patients, the 20 mg/m^2^ of AMR will be determined as MTD and RD. (3)‐2: If DLTs are confirmed in more than one of the additional three patients, the study will be considered to terminate.

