**FIGURE 2 tca14555-fig-0002:**
[figure not shown]
The schema of the method to determine RD and MTD in ACIST study. If DLTs are not observed in the initial three patients, we plan to add six patients. The 25 mg/m^2^ of AMR will be determined as MTD and RD. If DLTs are confirmed in one of the first three patients enrolled, we will add three additional patients at 25 mg/m^2^. If DLTs are confirmed in none of the additional three patients, we will add six additional patients. The 25 mg/m^2^ of AMR will be determined as MTD and RD. If DLTs are confirmed in more than one of the additional three patients, the 25 mg/m^2^ of AMR will be determined as MTD and the 20 mg/ml of AMR will be determined as RD. If DLTs are confirmed in more than two of the first three patients, we plan to add three patients to receive a reduced dose of 20 mg/m^2^. If DLTs are confirmed in none of the additional three patients, the 20 mg/m^2^ of AMR will be determined as MTD and RD. If DLTs are confirmed in more than one of the additional three patients, the study will be considered to terminate

All patients enrolled in the study will provide written informed consent, and the study will be conducted in accordance with the Declaration of Helsinki and Good Clinical Practice Guidelines. The study protocol was reviewed and approved by the clinical review board of Nagasaki University (CRB7180001). This study was registered in the Japan Registry of Clinical Trials (no. jRCT1071200033) on September 30, 2020.

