### Endpoints

The primary endpoint of the present study is to determine RD, and secondary endpoints are evaluating the response rate (RR), OS, progression‐free survival (PFS), MTD, DLTs and adverse effects. Efficacy will be assessed according to the Response Evaluation Criteria in Solid Tumors ver.1.1. PFS is defined as the time from the start date of chemotherapy to disease progression or death from any cause, whereas OS is defined as the time from the start date of chemotherapy to the last day confirmed to be alive or dead from any cause.

The Kaplan–Meier method will be used to estimate PFS and OS. Survival analysis will be conducted at the end of the follow‐up period. STATA SE version 16.1 (Stata Corp) will be used to perform analyses.

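### The dose-decision thresholds leave three DLT counts with no action, including 2 of the first 3 patients at 25 mg/m²

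*Protocol article*

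**What the plan says.** The Endpoints section states: "The primary endpoint of the present study is to determine RD". The rules that produce the RD are in Methods, Study design, numbered (1) to (3), and the text introduces them with "MTD and RD will be determined as shown in Figure 2".

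- **First three patients at 25 mg/m².** No DLT: rule (1) adds six patients and makes 25 mg/m² the MTD and RD. One DLT: rule (2) adds three more patients at the same dose. Rule (3), which opens the 20 mg/m² dose, is the only other branch: "If DLTs are confirmed in more than two of the first three patients, we plan to add three patients to receive a reduced dose".
- **Additional three at 25 mg/m², after one DLT.** No DLT: rule (2)-1 adds six patients and makes 25 mg/m² the MTD and RD. Rule (2)-2 is the only other branch: "If DLTs are confirmed in more than one of the additional three patients, the study will be finished", with 25 mg/m² as MTD and 20 mg/m² as RD.
- **Three at 20 mg/m².** No DLT: rule (3)-1 makes 20 mg/m² the MTD and RD. Rule (3)-2 is the only other branch: "If DLTs are confirmed in more than one of the additional three patients, the study will be considered to terminate".

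The Figure 2 legend repeats these thresholds at all three steps, for example "If DLTs are confirmed in more than two of the first three patients, we plan to add three patients" and "If DLTs are confirmed in more than one of the additional three patients, the 25 mg/m^2^ of AMR will be determined as MTD".

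**The concern.** Each decision looks at three patients, so the DLT count can only be 0, 1, 2 or 3, and a complete rule assigns one action to each. As worded, every step leaves one value out. The omitted values are ordinary ones: two DLTs among the first three patients, and two among six in total after expansion at 25 mg/m².

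These thresholds are the only decision rule the article gives for its primary endpoint. Read literally, the reduced dose is opened only if every one of the first three patients has a DLT. After two of three, no next step is defined. After two of six, no RD is defined. In either case the action would have to be chosen after the toxicities had been seen, which is what a pre-specified dose rule is meant to prevent. The study is multi-institutional, so different readers could also resolve the gap differently.

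**Working it through.** **Step 1: coverage of each count, read literally**

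| Decision | 0 DLTs | 1 DLT | 2 DLTs | 3 DLTs |
|---|---|---|---|---|
| First three, 25 mg/m² | rule (1) | rule (2) | **none** | rule (3) |
| Additional three, 25 mg/m² | (2)-1 | **none** | (2)-2 | (2)-2 |
| Three at 20 mg/m² | (3)-1 | **none** | (3)-2 | (3)-2 |

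No other part of the article supplies the missing cells. This result does not depend on any assumed DLT rate.

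**Step 2: how often a gap would be reached**

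The article states no DLT rate and no operating characteristic, so there is no figure of its own to reproduce. Let p be the true DLT rate at 25 mg/m² and q the rate at 20 mg/m². Both are assumed, with independent patients and cohorts of three as in the rules. Then:

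- Gap A, 2 of the first 3: 3p²(1−p)
- Gap B, 1 of the first 3, then 1 of the additional 3: [3p(1−p)²]²
- Gap C, 3 of the first 3, then 1 of 3 at 20 mg/m²: p³ × 3q(1−q)²

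For p = 0.30 and q = 0.20:

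- A = 3 × 0.09 × 0.70 = 0.1890
- B = (3 × 0.30 × 0.49)² = 0.441² = 0.1945
- C = 0.027 × (3 × 0.20 × 0.64) = 0.027 × 0.384 = 0.0104
- Total = 0.394

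| p | q | A | B | C | Total with no rule |
|---|---|---|---|---|---|
| 10% | 5% | 2.70% | 5.90% | 0.01% | 8.6% |
| 20% | 10% | 9.60% | 14.75% | 0.19% | 24.5% |
| 30% | 20% | 18.90% | 19.45% | 1.04% | 39.4% |
| 40% | 30% | 28.80% | 18.66% | 2.82% | 50.3% |
| 50% | 40% | 37.50% | 14.06% | 5.40% | 57.0% |

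The choice of q matters little. For any q from 0 to p, the totals are 8.6%, 24.3 to 24.7%, 38.3 to 39.5%, 47.5 to 50.3% and 51.6 to 57.1%.

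**Step 3: chance that the first three patients trigger the reduced dose**

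Read literally this is p³. With a threshold of two or more it is 3p²(1−p) + p³.

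| p | Literal | Two or more |
|---|---|---|
| 10% | 0.1% | 2.8% |
| 20% | 0.8% | 10.4% |
| 30% | 2.7% | 21.6% |
| 40% | 6.4% | 35.2% |
| 50% | 12.5% | 50.0% |

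**Step 4: check of the corrected thresholds**

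Use two or more for the first three patients and one or more for each later three. With p = q = 0.30 the paths are:

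- RD 25 mg/m²: 0.343 + 0.441 × 0.343 = 49.4%
- RD 20 mg/m² through (2)-2: 0.441 × (1 − 0.343) = 29.0%
- RD 20 mg/m² through (3)-1: 0.216 × 0.343 = 7.4%
- Termination considered, (3)-2: 0.216 × (1 − 0.343) = 14.2%

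These sum to 100%. Under the corrected wording the branches at each step are complementary, so nothing is left uncovered at any p or q.

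**The case against.** The strongest reply is that the meaning is plain. A split that runs none, one, then more must be meant to include two, and a split that starts at none must be meant to continue at one. On that reading no gap exists, and the probabilities above describe a trial nobody intends to run. **This is probably right about intent.** The percentages are therefore conditional on the wording being applied as published. It does not rescue the wording: the same form appears three times in the text and three times in the legend, and a safety threshold should not depend on readers overriding it.

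Second, the literal rules do not send more patients to a toxic dose. After two DLTs in the first three, neither rule (1) nor rule (2) applies, so nothing authorises further dosing at 25 mg/m². After one in the additional three, rule (2)-1 does not apply, so the extension is not authorised. **This stands.** The harm is an undefined next step and an undefined RD, not a rule that prescribes overdosing.

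Third, the text defers to Figure 2, whose image was not available, and the full protocol was not available either. Both may state the thresholds correctly. **This limits the claim to the published text and legend.** If the image is correct, the text and legend contradict it and still need changing.

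Fourth, the upper rates may be pessimistic. The abstract says "the initial dose of AMR 25 mg/m^2^ is expected to be tolerated and acceptable", and 25 mg/m² was the RD with once-daily radiotherapy in the earlier phase I study. **This is fair, so the 40% and 50% rows should carry less weight.** The 10% and 20% rows still give about 1 in 12 and 1 in 4. The gap at 20 mg/m² is minor, adding at most 5.4 percentage points in the scenarios tabulated.

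**Conclusion.** The concern holds. As published, the dose rule has no action for 2 DLTs in the first 3 patients, for 1 in the additional 3 at 25 mg/m² (2 of 6 in total), or for 1 of 3 at 20 mg/m². This is not detail that an article leaves to the full protocol: the rule is set out branch by branch, twice, with wrong thresholds, and it decides the primary endpoint.

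The existence of the gaps rests on enumeration alone. Their size rests on assumed DLT rates, independent patients and literal application. For rates of 10% to 30% at 25 mg/m², consistent with the dose being expected to be tolerable, the chance of reaching an undefined outcome is 8.6% to 39.4%. It reaches 57.0% at a rate of 50%. Nearly all of it comes from the two gaps at 25 mg/m². That the wording is a slip is an inference, supported by the fact that the same shift of threshold closes all three gaps. The point should be corrected because a dose-decision and safety threshold is affected and the correction costs almost nothing.

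**What to change.** - In rule (3) and the matching sentence of the Figure 2 legend, change the threshold for the first three patients to *two or more*.
- In rules (2)-2 and (3)-2 and the two matching sentences of the legend, change the threshold for the additional three patients to *one or more*.
- Confirm that the Figure 2 image and the full protocol carry the same thresholds, and correct them if they do not.
- If a different action was intended for 2 of the first 3, 1 of the additional 3 at 25 mg/m², or 1 of 3 at 20 mg/m², write that branch out explicitly instead.

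The cost is a wording correction in six sentences, plus the figure and full protocol if they share the error. No patients, visits or analyses are added.

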**FIGURE 2 tca14555-fig-0002:**
[figure not shown]
The schema of the method to determine RD and MTD in ACIST study. If DLTs are not observed in the initial three patients, we plan to add six patients. The 25 mg/m^2^ of AMR will be determined as MTD and RD. If DLTs are confirmed in one of the first three patients enrolled, we will add three additional patients at 25 mg/m^2^. If DLTs are confirmed in none of the additional three patients, we will add six additional patients. The 25 mg/m^2^ of AMR will be determined as MTD and RD. If DLTs are confirmed in more than one of the additional three patients, the 25 mg/m^2^ of AMR will be determined as MTD and the 20 mg/ml of AMR will be determined as RD. If DLTs are confirmed in more than two of the first three patients, we plan to add three patients to receive a reduced dose of 20 mg/m^2^. If DLTs are confirmed in none of the additional three patients, the 20 mg/m^2^ of AMR will be determined as MTD and RD. If DLTs are confirmed in more than one of the additional three patients, the study will be considered to terminate

All patients enrolled in the study will provide written informed consent, and the study will be conducted in accordance with the Declaration of Helsinki and Good Clinical Practice Guidelines. The study protocol was reviewed and approved by the clinical review board of Nagasaki University (CRB7180001). This study was registered in the Japan Registry of Clinical Trials (no. jRCT1071200033) on September 30, 2020.

### Inclusion criteria

(i) Histologically or cytologically confirmed SCLC (combined SCLC is acceptable); (ii) LD; (iii) age between 20 to 75 years; (iv) Eastern Cooperative Oncology Group Performance Status of 0 or 1 (v) regardless of measurable lesions; (vi) no prior chemotherapy; (vii) no multiple active cancers; (viii) latest clinical laboratory test within 14 days before registration meets the following criteria: (a) neutrophil count ≥1500 /μL, (b) platelet count ≥1.0 × 10^5^ /μL, (c) total‐bilirubin ≤1.5 mg/dL, (d) aspartate aminotransferase ≤100 U/L and alanine aminotransferase ≤100 U/L, (e) serum creatine ≤1.2 mg/dL, (f) SpO_2_ ≥ 92% (room air); (ix) radiologists expect sufficient preservation of respiratory function after chemoradiotherapy; and (x) written informed consent.

LD is defined as lesions limited to the ipsilateral thorax, contralateral mediastinum, and supraclavicular lymph nodes without malignant pleural or pericardial effusions.

### Exclusion criteria

(i) Resectable stage IA; (ii) presence of symptoms because of pericardial effusion; (iii) urgent radiation therapy is necessary because of superior vena cava syndrome; (iv) persistence of heart disease; (v) uncontrolled diabetes; (vi) uncontrolled hypertension; (vii) active systemic infection necessitating treatment; (viii) pregnant, possibly pregnant, postpartum within 28 days, breastfeeding, and males considering children; (ix) fever of 38.0°C; (x) mental disorder or symptoms interfering with daily life and inappropriate for enrollment; (xi) continuous intravenous or oral administration of steroids or immunosuppressants; (xii) hepatitis B surface antigen‐positive or hepatitis C virus antibody‐positive; (xiii) human immunodeficiency virus antibody‐positive (not necessarily examined); (xiv) interstitial pneumonia, pulmonary fibrosis, or emphysema confirmed by computed tomography; and (xv) other inappropriate complications.

### Interventions

#### Chemotherapy

In the first cycle, AMR 25 (or 20, if reduced) mg/m^2^/day (from day 1 to day 3) and cisplatin 60 mg/m^2^/day (day 1) will be administered. In the following three cycles, AMR 35 mg/m^2^/day (from day 1 to day 3) and cisplatin 60 mg/m^2^/day (day 1) will be administered (Figure 1).

#### Radiation therapy

AHTRT, as 1.5 Gy/time, twice daily, 5 days a week, 45 Gy in total, will be administered concurrently from day 2 of the first chemotherapy cycle (Figure 1). In addition to the three‐dimensional conformal radiation therapy, intensity‐modulated radiation therapy is acceptable. Calculating the actual value of V20 (volume of normal lung irradiated over 20 Gy compared to all lung volumes) or proportion of irradiation field for one lung is unnecessary before registration, and estimation by chest X‐ray or computed tomography is acceptable. To determine whether the desired respiratory function is preserved after radiotherapy, the target criterion of V20 is under 30%.

### Endpoints

The primary endpoint of the present study is to determine RD, and secondary endpoints are evaluating the response rate (RR), OS, progression‐free survival (PFS), MTD, DLTs and adverse effects. Efficacy will be assessed according to the Response Evaluation Criteria in Solid Tumors ver.1.1. PFS is defined as the time from the start date of chemotherapy to disease progression or death from any cause, whereas OS is defined as the time from the start date of chemotherapy to the last day confirmed to be alive or dead from any cause.

The Kaplan–Meier method will be used to estimate PFS and OS. Survival analysis will be conducted at the end of the follow‐up period. STATA SE version 16.1 (Stata Corp) will be used to perform analyses.

### Monitoring and follow‐up

Patients will be monitored twice yearly to ensure the accuracy and quality of the study. The principal investigator is responsible for compliance with the study protocol. The first three patients will be carefully monitored to determine whether the treatment was precisely conducted, data were collected, and serious nonconformities or adverse events occurred. Efficacy and toxicity will be followed up until the end of the follow‐up period.

## DISCUSSION

Several clinical trials have demonstrated the effects and toxicities of EP combined with AHTRT, exhibiting a median PFS between 15.4 and 18.8 months, median OS between 23.0 and 30.0 months, and manageable toxicities.^4^, ^5^, ^6^, ^11^ Although EP has been the standard regimen for patients with LD‐SCLC for two decades, novel therapeutic options are needed to further improve patient prognosis.

Regarding the combination of drugs other than EP with AHTRT, a phase III clinical study has compared EP and irinotecan plus cisplatin (IP) after induction of EP with AHTRT as consolidation therapy; however, three cycles of IP failed to improve OS when compared with three cycles of EP after one cycle of EP with concurrent AHTRT.^12^

In another study examining the consolidation of three cycles of AP after one cycle of EP with AHTRT, the authors documented an impressive 5‐year OS rate of 57.8%, suggesting the therapeutic potential of AP combined with AHTRT. The incidence of grade 3/4 neutropenia was 100%, whereas that of febrile neutropenia was 43%; however, all observed adverse effects were manageable with granulocyte‐colony stimulating factor support.^13^ It should be noted that the dose of AMR was set at 40 mg/m^2^ according to the RD from the phase I‐II study of AP for treatment‐naive ED‐SCLC,^14^ however, dose reduction was required in 33% of patients, implying that dose of 40 mg/m^2^ AMR might be too toxic for the patients with LD‐SCLC who will receive AP combined with AHTRT. Considering the toxicities associated with AMR, the RD of AMR with once‐daily TRT was evaluated from 20 mg/m^2^ in a dose‐escalation manner, and the RD of AMR was determined as 25 mg/m^2^ in our previous study.^7^ Following the introduction of twice‐daily irradiation, we plan to undertake a dose de‐escalation approach from 25 mg/m^2^ to determine the RD of AMR with twice‐daily AHTRT, based on our previous phase I study, which showed that doses of 25 mg/m^2^ AMR and 60 mg/m^2^ cisplatin are recommended for AP combined with TRT (2 Gy/day, once‐daily).^10^ We also set to raise the dose of AMR to 35 mg/m^2^ from second to fourth cycles of AP because AHTRT will finish during the first cycle of AP in this protocol. In a phase III study, which compared the efficacy of AP and that of IP in treatment naive Japanese patients with ED‐SCLC, the dose of AMR was reduced from 40 mg/m^2^ to 35 mg/m^2^ because of the high incidence of severe hematological toxicities.^15^ Furthermore, our retrospective study revealed that the real‐world incidence rate of febrile neutropenia among patients with thoracic malignancies that were treated with single‐agent AMR chemotherapy was 30%.^16^ Based on these findings for Japanese patients, the dose of 35 mg/m^2^ AMR from second cycle to fourth is predicted as the suitable dose in this protocol.

Sequential treatment with AMR or amurubicinol before ionizing radiation induces an additive radio‐enhancement effect in vitro.^17^ In addition, fractionation of a customary once‐daily dose into two treatments each day affords biological advantages, along with a high antitumor effect, resulting in the same total doses.^3^ The phase III CONVERT trial failed to demonstrate a survival advantage with high‐dose TRT when compared with standard twice‐daily TRT.^5^ Based on these findings, AP combined with twice‐daily AHTRT is expected to be a potential candidate for optimal treatment of LD‐SCLC.

Immunotherapy using immune checkpoint inhibitors (ICIs), such as programmed cell death 1 (PD‐1), programmed death‐ligand 1 (PD‐L1), and cytotoxic T‐lymphocyte‐associated protein 4, either as single agents or combined with cytotoxic chemotherapy, has revolutionized the treatment of several solid tumors, including SCLC.^18^ A recent study has shown that the addition of an anti‐PD‐1 antibody, pembrolizumab, to AMR for relapsed SCLC could afford a remarkable ORR of 52% and PFS rate of 14.4% at one year,^19^ indicating the promising effect of AMR when combined with ICIs. For some patients with LD‐SCLC who would benefit from ICIs, a combination with AP may be an optimal strategy in the future.

In summary, the present study is the first to evaluate AP combined with AHTRT for LD‐SCLC from the first chemotherapy cycle. This study will reveal whether AP combined with twice‐daily AHTRT could be tolerated and is an optimal regimen for LD‐SCLC.

## REGISTRATION DETAILS

This study was registered in the Japan Registry of Clinical Trials (no. jRCT1071200033) on September 30, 2020.
